### Ethics and registration

All protocols and patient informed consent for this study have been approved by the Research Ethics Board (REB) of The Royal's Institute of Mental Health Research (REB# 2,019,071 approved on August 7, 2019). Significant changes to this study (e.g., any procedure, inclusion/exclusion criteria) will only take place after Ethics Committee’s approval. The trial is registered on https://clinicaltrials.gov/ct2/home (#NCT04142996). All in-person study procedures will take place at the University of Ottawa Institute of Mental Health Research at The Royal.

### Participants

A maximum of 256 participants (128 per group; biological male or female, ≥ 18 years-old) with a diagnosis of a major depressive episode (MDE) will be recruited through advertisements posted at the Royal Ottawa Mental Health Centre (ROMHC) and medical clinics in the Ottawa/Gatineau region. All participants must have a referral from their treating physician (e.g., psychiatrist or general physician). Multiple strategies will be used to ensure participant retention. Specifically, communication and engagement will be maintained through regular contact, education and feedback channels. Participants will be compensated for their involvement in the study. Monitoring will be diligent, with frequent assessments and adherence tracking. In cases of discontinuation or protocol deviations, exit interviews, data collection extensions and adverse event reporting will ensure that data is obtained.

### Randomization and blinding

Participants are randomized (1:1 ratio) using the study randomizer software (https//www.studyrandomizer.com). A permutated block is used to randomize participants into the treatment groups. Participant stratification is based on the following variables: 1) age (< 65 or ≥ 65 years-old), 2) depression (unipolar or bipolar), 3) comorbid generalized anxiety (yes or no), 4) comorbid post-traumatic stress disorder (yes or no), and 5) biological sex (male or female). Upon entering these participant characteristics, the software provides a number (e.g., 0 or 1) that corresponds to a treatment group in which experimenters and participants are blinded to. Participants will remain assigned to their designated group until the treatment concludes.

This study is a two-arm double-blind trial as neither the participants nor the outcome assessor, care provider and data analysts will know the condition assigned to the participants. The master randomization list of the treatment blinding will be kept by a scientist of the research centre that is not involved in the project. This can be broken in case of emergency (e.g., severe adverse events such as seizure induced by treatment) and they can then inform required medical professionals directly if necessary. Directly involved research staff will be blinded (including the principal investigator and study psychiatrists).

### Unilateral and bilateral treatment – iTBS and cTBS

The TBS parameters used in this study are consistent with previous determined guidelines [90]. Specifically, TBS will consist of triple-pulse 50-Hz bursts applied at a rate of 5 Hz using a MagPro X100-MagOption stimulator device (Magventure, Farum, Denmark). iTBS will be delivered through a B70 coil and cTBS will be delivered using an active/sham B65 figure-of-eight cooled-coil (Magventure, Farum, Denmark). Unilateral TBS consists of 40 s of sham cTBS applied to the right DLPFC followed by 190 s of iTBS (i.e., excitatory-inducing) over the left DLPFC. Bilateral sequential TBS will consist of 40 s of cTBS (i.e., inhibitory inducing) over the right DLPFC followed by 190 s of iTBS over the left DLPFC. Stimulation intensity for both iTBS and cTBS will be 80% of the individual's active motor threshold (AMT) assessed with single-pulse TMS (for AMT protocol, see *Single- and Paired-Pulse TMS* section below). Magnetic resonance imaging (MRI) -assisted neuronavigation will ensure proper coil position and targeting of the participants’ DLPFC. The TMS coil will be positioned with the handle pointing backwards and at a 45-degree angle from the midline and centered against the left and right DLPFC locations (e.g., Fig. 1). The DLPFC stereotactic coordinates (MNI-152) are: x = -38, y = 44, z = 26 [37].

To ensure the sham stimulation mimics the somatosensory components experienced during active TBS stimulation (e.g., pulse noise, tingling, tapping sensation), the sham coil will produce the same auditory feedback and will deliver synchronous electrical pulses to the scalp through electrodes. To ensure double-blinding, participant IDs will be entered in a software-controlled switch that will automatically select the previously randomized TBS condition (active or sham) created by a team member not involved in treatment and data collection. To evaluate the integrity of the blinding procedure, at the end of each treatment phase (i.e., initial and maintenance phase), participants will complete a questionnaire to assess their opinion on whether they received active stimulation on one or both sides of their head. A questionnaire assessing 12 common acute side-effects of rTMS (e.g., headache, pain, fatigue) will be given after each TBS session to monitor potential side effects. These questions are: 1) in the 24 h following your most recent TMS session, did you experience back or neck pain? 2) pain or discomfort at the stimulation site? 3) headache? 4) tinnitus? 5) dizziness? 6) fatigue (more than usual)? 7) insomnia? 8) anxiety or agitation? 9) nausea? 10) vomiting? 11) migraine aura? 12) abnormal sensations?". Participants rate symptoms on a scale ("none," "very mild," "mild," "moderate," or "severe") and indicate if they attribute this rating to the treatment (“yes”, “no"). A post-treatment feedback questionnaire will be administered at the end of the first and last TBS session in the initial treatment phase to assess the quality of the study and include questions such as 1) "did you feel welcome when coming into the lab?", 2) "was everything thoroughly explained to you prior to treatment?", 3) "did you feel that you knew what to expect coming into the study?", 4) "how can we improve to make the experience better?". Participants rate these questions as “not at all," “small degree," “neutral," “moderate degree," or “high degree." If there are any adverse events recorded during these questionnaires or during any study visit, we will record them and report them to the REB.

### Study outcomes

#### Clinical outcomes

Clinical outcomes will be determined using self-report questionnaires and clinical interviews conducted by trained research personnel. Several standardized questionnaires were selected to provide a comprehensive understanding of depressive-related symptoms and will serve as outcomes of treatment response. See Table 3 for all clinical outcomes collected, their description/purpose, outcome value, and timepoint of collection.

##### Primary outcome measure

Response to treatment will be primarily defined as a ≥ 50% reduction in pre-treatment symptom severity as measured by the HRSD-17 score. Treatment remission will be defined as a HRSD-17 score ≤ 7. These definitions of treatment response and remission are based on recent literature assessing the effects of rTMS in individuals with depression [33, 37, 38, 91, 92].

##### Secondary outcome measure

For secondary analyses response to treatment will be defined as a ≥ 50% reduction in pre-treatment symptom severity as measured by the mean 16-item Quick Inventory of Depressive Symptoms–self report (QIDS-SR_16_) score and Montgomery–Asberg Depression Rating Scale (MADRS). Remission will be defined as a QIDS-SR_16_ score of ≤ 6 and a MADRS score < 12. Additionally, other secondary outcomes will include effect of treatment on anxiety (Beck Anxiety Inventory), symptoms of mania (Young Mania Rating Scale, Altman Self-Rating Mania Scale), quality of life (Quality of Life Enjoyment and Satisfaction Questionnaire), symptoms of post-traumatic stress disorder (Post-traumatic Stress Disorder Checklist for DSM-5), and well-being (Short Warwick Edinburgh Mental Well-Being Scale).

#### MRI – Brain connectivity and metabolism

Within two weeks prior to treatment onset, whole brain MRI from participants will be collected to assist with the targeting of the DLPFC, TMS-EEG, and TBS sessions. MRI scans will be performed using a 3 T Siemens mMR Integrated Whole-Body PET/MR Scanner and 32-channel head coil (Ceresensa Inc.). First, a T1-weighted (MEMPRAGE, 1mm^3^ isotropic voxel-size, lasting approximately 6 min) scan will be collected, followed by two runs of BOLD-EPI (TR = 2300 ms, 27 mm^3^ isotropic voxel-size, 183 volumes/run, 8 min per run) to collect resting state images. Lastly, a single voxel MRS scan will be collected using the GABA-edited MEGA-PRESS sequence [93] with the following parameters: TR = 2000 ms, TE = 68 ms, acquisition bandwidth = 2000 Hz, pulse placement edit-on/edit-off = 1.9/7.5 ppm, number of excitations edit-on/edit-off = 64/64 for a total of 128 averages. The voxel will be positioned over the bilateral ACC (35 × 20x20mm) using the T1 images and according to previous literature [94, 95]. Two MEGA-PRESS acquisitions edited with GABA will be acquired (4.36 min each) as well as two water-unsuppressed reference scans (0.48 min each).

Standard resting state fMRI data preprocessing and denoising steps will be conduted using fMRIPrep (https://fmriprep.org/) and the functional connectivity toolbox (CONN: www.nitrc.org/projects/conn). Preprocessing steps will include correction for motion, functional realignment and unwarping, direct normalization into the MNI common space, and smoothing with a spatial filter. Seed region-of-interest will be defined as a 10 mm radius circle around the TMS target regions. Correlations between the residuals in the seed and the whole brain time series will be calculated for each fMRI run separately. Runs will be combined by calculating a voxel/vertex–wise mean of z-transformed r-values. Resting state fMRI connectivity values between the seed and the ACC will be extracted with a region of-interest in the ACC (dorsal, pregenual, subgenual). For MRS data, post-processing of MRS signals will be conducted using Matlab scripts (MathWorks, USA) and LCModel [96]. The LCModel software will be used to quantify the concentrations of GABA and Glutamate + Glutamine (Glx) in the ACC. Individual resonances having Cramer-Rao Lower Bounds greater than 20% will be omitted from further investigation. Moreover, exclusion of data will be made on spectra that exhibit obvious artifacts, such as large head motions, lipid contamination (huge peak near 1 ppm) and poorly shimmed data. Post-processing will include phase correction and frequency drift correction of the individual sub-spectra utilizing residual water as a reference, followed by the average of the phase- and frequency-corrected spectra. GABA and Glx levels will be obtained from difference and “EDIT OFF” spectra, respectively.

#### Single- and paired-pulse TMS – corticospinal excitability

Participants’ MRI will be uploaded into the neuronavigation software (Brainsight, Rogue Research Inc, Montreal, QC) to assist with visualization of participants’ primary motor cortex and guide coil position during the TMS and TBS sessions (i.e., neuronavigated MRI-assisted TMS). Single-pulse TMS will be performed using a MagPro X100-MagOption Stimulator with a 70 mm figure-of-eight coil (MagVenture, Denmark) to elicit MEPs in the contralateral first dorsal interosseous (FDI) muscle. Biphasic pulses will be used to determine treatment active thresholds, and monophasic pulses will be used to determine resting thresholds for TMS biomarkers. MEPs will be collected using the neuronavigation built-in electromyography (EMG) system (Brainsight, Rogue Research). Surface electrodes (Kendall™, Cardinal Health, Waukegan, USA) placed over the belly of the FDI muscles will collect MEPs of both hands. The reference and ground electrodes will be placed in the interphalangeal joint of each index fingers and on any prominent bone (e.g., olecranon, medial/lateral epicondyle, styloid process), respectively, ipsilaterally to the tested FDI muscle.

Using the uploaded MRI in the neuronavigation software, a grid with targets (9 × 9, 3 mm distance between targets) was a priori centered on the central sulcus. Each target received three-five suprathreshold stimulations, and the "hotspot" for the contralateral FDI was determined based on the target that yielded the highest average peak-to-peak MEP amplitude. Next, participants' resting and active motor thresholds (RMT and AMT, respectively) will be determined using the relative frequency estimation method (for detailed protocol see; [97]. In brief, the least amount of stimulation intensity to elicit five out of ten 50 µV amplitude MEPs during complete relaxation and 200 µV amplitude MEPs while participants perform 10% of their maximal pinch contraction determines RMT and AMT, respectively. RMT and AMT will be used to normalize the following experiments across participants and to individualize the stimulation intensity for the TBS treatment, respectively (e.g., % of RMT and AMT).

TMS biomarkers indexing corticospinal inhibition and excitation, such as MEP amplitudes, short- and long-interval intracortical inhibition (SICI, LICI, respectively), and intracortical facilitation (ICF), will be collected during the first TMS session after motor threshold are determined. Baseline MEP amplitudes will be collected with single-pulse TMS at a stimulation intensity of 130% of RMT. SICI, LICI, and ICF will be assessed with paired-pulse TMS, where the conditioned stimulus precedes a second stimulus that is separated by an interstimulus interval (ISI). For SICI and ICF, the conditioned stimulus, delivered at 80% of RMT, is followed by a test stimulus, delivered at 130% of RMT, at an ISI of 2 and 12 ms, respectively. For LICI, both the conditioned and test stimuli are delivered at 130% of the RMT, and the ISI is 100 ms. Degree of inhibition is measured as the ratio between the single-pulse TMS elicited- and the paired pulse-TMS elicited- MEPs (e.g., = conditioned/unconditioned MEP); lower ratios signify higher degree of intracortical inhibition [97]. A total of 60 MEPs will be collected; 20 single- and 60 paired-pulses (20 per paired-pulse measure).

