**Single and Paired-Pulse TMS**	RMT	Assesses cortical excitability via indirect activation of cortical interneurons (I-wave)	M1 (bilaterally)	Used to normalize the following TMS experiments (e.g., % of RMT)
	AMT	Cortical excitability via direct activation of corticospinal tract neurons (D-wave)	M1 (bilaterally)	Used to normalize the TBS treatment intensity (e.g., % of AMT)
	MEP Amplitude	Capacity of the corticospinal tract in recruiting neurons from faster temporospatial summation at cortico-motoneuronal synapses. Reflects glutamatergic (NMDA- and AMPA-receptor) activity	Left M1	Used as unconditioned MEP (i.e., test MEP), to calculate degree of inhibition during paired-pulse experiments (e.g., degree of inhibition = conditioned/unconditioned MEP)
	SICI	Short-interval intracortical inhibition primarily influenced by GABA_A_-receptor activity	Left M1	To investigate TMS biomarkers of treatment response examined with correlation analysis between baseline TMS and pre-post changes in clinical measures
	LICI	Long-interval intracortical inhibition primarily influenced by GABA_B_-receptor activity	Left M1	
	ICF	Intracortical facilitation primarily influenced by glutamatergic (NMDA- and AMPA-receptor) activity	Left M1	
**TMS-EEG**	TEP and ERSP	Assesses trans-synaptic activation of local and distal cortical networks mediated by excitatory and inhibitory cortical circuitry	TMS performed on the left and right DLPFC (120% of RMT) and TEP/ERSP are recorded from the DLPFC (primarily) and whole brain (exploratorily)	To investigate TMS-EEG biomarkers of treatment response, examined with correlation analysis between baseline TEPs/ERSPs and pre-post changes in clinical measures. To investigate cortical changes from treatment, examined with repeated-measures analysis [pre- vs post initial treatment (week 4, or week 6 for non-remitters), vs post maintenance phase (e.g., final week (week 24)]
**MRI**	Structural MRI	Assesses anatomy and morphology of CNS structures	Whole brain	To be uploaded into the neuronavigation software to assist with the location and targeting of the M1 and DLPFC during TMS assessments and TBS treatment, respectively (MRI-assisted TMS)
	MRS	Availability of neurotransmitters within the CNS (GABA and Glutamate)	Bilateral ACC	To investigate biomarkers of treatment response, examined with correlation analysis between baseline values and pre-post changes in clinical measures

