In our study, we are performing typical single- and paired-pulse TMS experiments to assess biomarkers of intracortical inhibition and excitation that are primarily, but not exclusively, mediated by GABAergic and glutamatergic neurotransmission, respectively [97]. Specifically, we will collect motor thresholds (RMT and AMT), biomarkers of cortical excitation (MEP amplitudes and ICF), and biomarkers SICI and LICI [97]. These biomarkers are of particular importance since previous TMS studies have shown that they are sensitive to abnormalities associated with MDD and related symptoms (e.g., cognitive impairments, mood alterations) [128]. For instance, studies investigating TMS motor thresholds in depressive disorders have shown reduced corticospinal excitability in the left cortex [129, 130] and interhemispheric imbalance, i.e., lower and higher excitability in the left and right cortex, respectively [131]. Delivering rTMS to excite the DLPFC has shown to revert this lowered excitability and reduce interhemispheric asymmetries, effects that were associated with clinical improvements [50]. As for the TMS biomarkers indexing GABAergic-mediated corticospinal inhibition (e.g., SICI, LICI) [97], previous studies have suggested a possible cortical disinhibition (i.e., decreased SICI) in the left hemisphere in MDD [132, 133]. These findings are interesting since outside pathology, excitation and inhibition are not mutually exclusive; lower excitation is typically followed by higher inhibition and vice-versa [64]. The fact that this does not seem to be the case in MDD points to the value of TMS-assessing both inhibitory and excitatory circuitry for a better comprehension of the treatment induced-neurophysiological effects and to identify complementary biomarkers of treatment response in MDD. The limitation of relying solely on TMS-induced MEPs to investigate the effects of interventions not focusing on the motor cortex (i.e., focusing on the DLPFC) is that this brain region is not amongst the most relevant CNS structures involved in symptoms of MDD and is not the targeted brain region of this treatment. Complementary to MEPs, we hope to improve our treatment predictability by including other neurophysiological assessments such as TMS-EEG and MRI. These techniques will help us to investigate the TBS-induced neurophysiological changes within the treatment-targeted region (i.e., DLPFC) and connected CNS structures closely associated with depressive symptoms (e.g., ACC).

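### The exploratory SICI, LICI and ICF correlations share one unconditioned MEP and name no adjustment for it, so a single amplitude effect could read as several transmitter-specific predictors

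*Protocol article*

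**What the plan says.** **The measure.** In the protocol article, Single- and paired-pulse TMS, "Degree of inhibition is measured as the ratio between the single-pulse TMS elicited- and the paired pulse-TMS elicited- MEPs", written as conditioned over unconditioned. The test intensity is tied to threshold, not to a target response size: "Baseline MEP amplitudes will be collected with single-pulse TMS at a stimulation intensity of 130% of RMT".

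**The shared denominator.** Table 4 gives the purpose of the MEP amplitude row as "Used as unconditioned MEP (i.e., test MEP), to calculate degree of inhibition during paired-pulse experiments". The only unconditioned MEPs described are the 20 single pulses, with 20 paired pulses for each of SICI, LICI and ICF.

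**The labels.** Table 4 describes SICI as "Short-interval intracortical inhibition primarily influenced by GABA_A_-receptor activity" and LICI as "Long-interval intracortical inhibition primarily influenced by GABA_B_-receptor activity". It attributes ICF to glutamatergic activity, and MEP amplitude likewise.

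**The analysis.** Table 4 gives the reason for collecting SICI as "To investigate TMS biomarkers of treatment response examined with correlation analysis between baseline TMS and pre-post changes in clinical measures"; the cells for LICI and ICF are empty and appear to share this entry. Predictors of treatment response calls the correlations exploratory and specifies Pearson or Spearman coefficients. It also plans regressions with MRI, TMS and TMS-EEG measures as predictors, plus a list of demographic and clinical control variables. That list does not name MEP amplitude and is left open-ended. The Discussion treats amplitude as a marker in its own right: "biomarkers of cortical excitation (MEP amplitudes and ICF").

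**The concern.** A ratio is free of its denominator only if the numerator scales in exact proportion to it. With test intensity fixed at a percentage of threshold, the unconditioned MEP differs between people. If the conditioned MEP rises less than proportionally, each ratio falls as amplitude rises. Sampling error in the 20 shared pulses also enters all three ratios with the same sign.

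If amplitude is itself related to clinical change, the ratios inherit that relation. Three correlations would then look like agreement between separate inhibitory and excitatory systems when they have one source. The reverse is also possible: an amplitude effect of opposite sign can cancel a real paired-pulse effect. Predictors of response are among the aims listed under Study objectives, and the Discussion wants them to guide selection of participants for TBS, so the attribution matters even in an exploratory analysis.

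**Working it through.** **The plan's own figure.** Sample size gives n = 30–39 for regressions with 3–6 variables (f² = 0.43, power 0.80, α = 0.05). A noncentral F test with λ = f²·N and df = (u, N − u − 1) gives 30, 33, 36 and 39 for u = 3, 4, 5 and 6, which reproduces the range.

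**Inputs from the article.** n = 158 (Sample size), 20 pulses per condition, two-sided α = 0.05.

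**Assumed inputs, not in the article.** Trial-to-trial CV 0.6; between-person SD 0.7 for log MEP and 0.5 for the log paired-pulse response; amplitude–outcome correlation ρ = 0.2 or 0.3; scaling power b = 1, 0.8 or 0.6; no true effect of any paired-pulse marker.

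**Model.** log U = u + e₁ and log C = b·u + v + e₂, so log(C/U) = (b − 1)u + v + e₂ − e₁. Each error variance is ln(1 + 0.6²/20) = 0.0178.

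- Variance of the log ratio: (b − 1)²·0.49 + 0.25 + 2·0.0178
- Its correlation with outcome: r = ρ(b − 1)·0.7 / SD
- Chance of p < 0.05: normal approximation with mean z = atanh(r)·√155

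| b | variance | SD | r at ρ = 0.2 | rate | r at ρ = 0.3 | rate |
|---|---|---|---|---|---|---|
| 1 | 0.286 | 0.534 | 0 | 5% | 0 | 5% |
| 0.8 | 0.305 | 0.553 | −0.051 | 10% | −0.076 | 16% |
| 0.6 | 0.364 | 0.603 | −0.093 | 21% | −0.139 | 41% |

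Simulation of the same model with Pearson tests gives 5 / 9 / 21% and 5 / 15 / 42%. Spearman tests at ρ = 0.3 give 5 / 15 / 38%. At ρ = 0.1 the rates for b = 0.8 and 0.6 are only 6% and 9%. At n = 79 (one arm) and ρ = 0.2 they are 6.5% and 12%.

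**Do the markers agree spuriously?** The correlation between two ratios is [(b − 1)²·0.49 + 0.0178] / variance, which is 0.06, 0.12 and 0.26 for b = 1, 0.8 and 0.6. With Spearman tests at ρ = 0.3 and n = 158, the chance that at least two of three markers reach p < 0.05 is 1 / 8 / 34%. The chance of at least one is 14 / 38 / 70%, of which 1 − 0.95³ = 14% is ordinary multiplicity.

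**Masking.** Let one marker have a real correlation of 0.25 with outcome through v, opposing the amplitude effect at ρ = 0.3. Then r = [(b − 1)·0.7·0.3 + 0.5·0.25] / SD:

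- b = 1: 0.125/0.534 = 0.234, power about 84%
- b = 0.8: 0.083/0.553 = 0.150, power about 47%
- b = 0.6: 0.041/0.603 = 0.068, power about 14%

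**After adjustment.** Measured log U captures 0.49/(0.49 + 0.0178) = 96% of the variance tied to true amplitude, so conditioning on it removes nearly all of the (b − 1)u term. Simulated per-marker rates return to about 4–6%. At proportional scaling, where adjustment is not needed, power for a real effect of 0.25 is 85% with it and 85% without.

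**Side observation.** The pulse count does not add up: "A total of 60 MEPs will be collected; 20 single- and 60 paired-pulses (20 per paired-pulse measure"), but 20 + 3 × 20 = 80. This should be reconciled. It does not affect the point, because the calculation uses the per-condition counts.

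**The case against.** **The regressions may already handle it.** A reader might infer that the plan adjusts for amplitude nowhere. The documents do not support that. TMS measures are entered as regression predictors, the article counts MEP amplitude among its TMS biomarkers, and the list of control variables is open-ended. This stands, so the point is confined to the correlations, with the regressions described as uncommitted. Models sized for 3–6 variables leave limited room, so amplitude could be dropped.

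**The harm is conditional.** It needs both an amplitude–outcome association and less-than-proportional scaling, and the article gives no figure for either. This stands; the size is a range that includes no effect.

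**The tests are not invalid.** When both conditions hold, the ratio really is correlated with outcome, so rejecting zero correlation is correct, and the ratio carries predictive information. This stands. The error lies in attributing the result to a specific mechanism.

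**The labels are hedged.** Table 4 and the Discussion attribute each marker to its transmitter primarily, not exclusively, and MEP amplitude and ICF share a glutamatergic label. So the mislabelling bites mainly for SICI and LICI. The hedge concerns transmitters, though, not a shared denominator.

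**Covariate detail belongs in an analysis plan.** That would hold if the article were silent. It states the metric, the common denominator and the type of test, so the remedy changes a stated method. The ratio is a referenced method, and the fix does not forbid reporting it.

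**Conclusion.** The point holds for the exploratory correlations. Under the assumed values at n = 158, with scaling power between 0.8 and 0.6, a marker with no effect of its own is flagged about 9–21% of the time at an amplitude–outcome correlation of 0.2 and 15–42% at 0.3, against 5% nominal. There is no inflation if scaling is proportional or amplitude is unrelated to outcome.

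Much larger rates, above 80% per marker, arise only if the conditioned MEP does not depend on the unconditioned one at all. A reader might extend that case to all three markers. A floor may be plausible for LICI but is not credible for ICF, which is facilitation, so those figures should not be used as the size of the problem.

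Priority is low. The correlations are labelled exploratory, the predictor hypotheses in Table 1 do not name SICI, LICI or ICF, and the primary HRSD-17 comparison is untouched.

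**What to change.** In Predictors of treatment response and in Table 4:

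- Test each log paired-pulse ratio against clinical change with log unconditioned MEP amplitude as a covariate, that is, as a partial correlation.
- Include unconditioned MEP amplitude in any regression that contains SICI, LICI or ICF.
- Report MEP amplitude as a predictor in its own right.
- Keep the raw-ratio correlations as descriptive results.

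No new data are needed. The cost is one degree of freedom per model; by the plan's own regression calculation, each extra variable between 3 and 6 adds 3 participants, well inside the planned sample. Adjusted results are slightly less directly comparable with papers that correlate raw ratios, which the descriptive results cover.
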